## Abstract

**Introduction:**

Many people with psychosis find the world very frightening. It can be difficult for them to do everyday things—for example, walking down a busy street, travelling on a bus or going to the shops. Sometimes, the fears are so great that individuals rarely leave their homes. gameChange virtual reality therapy is designed to reduce this agoraphobic avoidance. In gameChange, users practise going into computerised immersive versions of ordinary situations. A virtual therapist guides users through the programme. A mental health worker also supports people. People normally do six sessions of gameChange, but now they can do more as headsets can be left with many people. We originally tested gameChange with 346 patients with psychosis. People saw a significant reduction in their fears. People with the most severe problems made the biggest improvements. This led to gameChange receiving National Institute for Health and Care Excellence (NICE) Early Value Assessment (EVA) approval for its use with patients with psychosis who have severe agoraphobic avoidance. NICE EVA approval is conditional on further evidence generation. We aim to carry out a real-world trial of gameChange used in the NHS. The overall aim is to gather evidence on the four essential areas (clinical benefits on agoraphobia, level of engagement and adherence, healthcare resource use, adverse effects) and the two further supporting areas (health-related quality of life, generalisability) identified in the NICE evidence generation plan for gameChange.

**Methods and analysis:**

200 patients with psychosis and severe agoraphobic avoidance will be randomised (1:1) to receive gameChange in addition to treatment as usual (TAU) or to a waitlist control group receiving TAU. Assessments will be conducted blind to group allocation at baseline, 8 weeks (end of treatment) and 26 weeks (follow-up). The trial will be embedded in services in at least seven National Health Service (NHS) trusts across England. The primary outcome is agoraphobic avoidance at 26 weeks assessed with the Oxford Agoraphobic Avoidance Scale. The secondary clinical outcomes are agoraphobic distress, paranoia and social contacts. There will be tests of moderation of the main clinical outcome. Treatment acceptability, adverse effects and cost-effectiveness will also be assessed. The target estimand is the treatment policy estimand and all primary and secondary analyses will be carried out incorporating data from all participants including those who do not complete treatment.

**Ethics and dissemination:**

The trial has received ethical approval from the NHS Health Research Authority and Health and Care Research Wales (25/WA/0081). A key output will be the evidence needed for a NICE guidance update on gameChange and a clear recommendation concerning future routine use in the NHS.

**Trial registration number:**

ISRCTN79060696.

Strengths and limitations of this studyA strength of this randomised controlled trial of gameChange virtual reality is that it is designed to collect information across multiple domains: clinical efficacy, level of engagement and adherence, healthcare resource use, adverse effects, health-related quality of life and generalisability.To enhance the generalisability of the results, the trial will be embedded in multiple psychosis services across the country.The trial will not be able to determine the components of gameChange that lead to clinical benefits.The trial is only powered to detect moderate improvements with treatment in agoraphobic avoidance.

## Introduction

 Psychotic conditions—non-affective or affective—are known as severe mental health conditions. They can cause considerable personal distress to patients and their families. The NHS Long Term Plan^1^ has committed to improving access to evidence-based psychological therapies for people diagnosed with severe mental health disorders.

For many patients diagnosed with psychosis, everyday situations can become anxiety-provoking. Patients may fear, for example, negative judgements, observation, embarrassment, failure, rejection, panicking, deliberate social or physical harm from others, or being unable to cope with voices. The end result is that patients can avoid, or find intensely anxiety-provoking, everyday situations such as walking down the street, going to a local shop or getting on a bus. Patients may find it difficult to even leave their home. In effect, individuals are experiencing symptoms of agoraphobia. We view agoraphobic avoidance of everyday situations as a final common pathway for a variety of fears experienced by many patients with psychosis. In a survey of 1809 patients with non-affective psychosis attending NHS mental health services, we found anxious avoidance at agoraphobic levels for 64.5% of patients.^2^

We harnessed a consumer technology, virtual reality (VR), to help people in this patient group who were experiencing such difficulties. In our automated psychological therapy, gameChange, patients can practise overcoming their difficulties in simulations of the everyday situations that they fear. The automation of therapy in gameChange means that it can be supported by a range of NHS staff and require less of their time. gameChange is a cognitive treatment that aims for patients to relearn safety by testing their fear expectations. Within the VR environments, a virtual coach guides the person through the treatment. When first entering VR, the patient goes into the coach’s virtual office and is guided in how to use VR. At the beginning of the first session, the virtual coach explains the rationale behind the treatment, and the participant selects one of the six VR scenarios (eg, leaving the home, getting on a bus, ordering a coffee or tea in a café). Each scenario comprises five levels of difficulty and participants work their way through the tasks in each level.

Two outcome papers have been reported from a randomised controlled clinical trial with 346 patients with psychosis.^3 4^ These show that for any patient with psychosis who has agoraphobia symptoms, there is a significant reduction in fears at the end of treatment. However, a moderation analysis revealed that it was patients with severe agoraphobia and the highest overall mental health symptoms who had the largest gains both post-treatment and 6 months later. It is notable that, 6 months post-treatment, the 6-week gameChange intervention in patients with severe agoraphobia reduced agoraphobia to a large extent (effect size=0.8), reduced paranoia to a moderate extent (effect size=0.4) and improved quality of life to a moderate extent (effect size=0.5). No patient serious adverse events (SAEs) during the trial were linked with gameChange. A peer-led qualitative evaluation reported great enthusiasm for the approach from trial participants.^5^ A paper on satisfaction and side effects showed high satisfaction ratings and low occurrence of side effects that did not affect treatment outcomes or uptake.^6^ And a health economic evaluation^7^ indicated that gameChange may lower costs from an NHS and social care perspective and, by reducing informal caring, from a wider societal perspective too. The analysis also suggested that gameChange may be cost-effective against National Institute for Health and Care Excellence (NICE) thresholds for value per quality-adjusted life-year (QALY) gained.

On the basis of the randomised controlled trial results, gameChange obtained NICE Early Value Assessment (EVA) for medtech approval for use in the NHS: ‘gameChangeVR (a VR technology) can be used in the NHS while more evidence is generated, to treat severe agoraphobic avoidance in people with psychosis aged 16 and over. It should be used with the support of a mental health professional’. The approval is for use for patients diagnosed with psychosis who have severe agoraphobic avoidance (ie, the group that the moderation analysis indicates benefits most). NICE EVA approval is conditional on further evidence generation. The current project is designed to address the evidence gaps identified in the NICE EVA of gameChange.

### Aim and objective

The overall aim is to gather evidence on the four essential areas (clinical benefits on agoraphobia, level of engagement and adherence, healthcare resource use, adverse effects) and the two further supporting areas (health-related quality of life, generalisability) identified in the NICE evidence generation plan for gameChange.

#### Clinical benefits

Primary clinical question: For NHS patients diagnosed with psychosis and having severe agoraphobia, does gameChange when added to treatment as usual (TAU), compared with TAU, lead to a reduction in severe agoraphobic avoidance at 6 months?

Secondary questions:

Compared with usual care, does the addition of gameChange lead to reductions in paranoia?

Compared with usual care, does the addition of gameChange increase the number of social contacts outside the home?

What are the recovery and relapse rates in agoraphobic avoidance in each arm of the trial (as assessed by the bands of the Oxford Agoraphobic Avoidance Scale (O-AS), which is the primary outcome measure)?

#### Level of engagement and adherence

Primary question: What are the levels of engagement and adherence with gameChange?

#### Healthcare resource use

Primary question: What are the total costs of gameChange?

Secondary question: What are the standard care costs associated with gameChange compared with standard care alone?

#### Adverse effects

Primary question: Are there any SAEs linked to the use of gameChange?

Secondary question: What proportion of patients have side effects from gameChange and do these interfere with adherence or outcomes?

#### Health-related quality of life

Primary question: Is gameChange cost-effective?

Secondary question: Compared with usual care, does the addition of gameChange lead to improvements in quality of life?

#### Generalisability

Primary question: Is gameChange an acceptable treatment for patients?

Secondary questions:

Are gameChange treatment outcomes moderated by socio-demographic or clinical factors (eg,age, gender, ethnicity, location, diagnosis)?

Do levels of engagement and adherence vary by sociodemographic or clinical factors?

## Methods and analysis

### Trial design and flow chart

The design is a multicentre two-arm waitlist randomised controlled trial testing the addition of gameChange to TAU against TAU. We wish to determine the ‘in toto’ benefits of the VR intervention when added to standard care (ie, the total effect for patients if implemented in the NHS). 200 patients will be randomised to one of two conditions: gameChange (added to TAU) or a waitlist control group (continuing to receive TAU). gameChange will be provided for 8 weeks with a staff member. Assessments will be conducted blind to group allocation at 0, 8 and 26 weeks. The waitlist control group will also be assessed after treatment (34 weeks). A summary of the trial design can be seen in figure 1. The trial will take place in seven sites: Avon and Wiltshire Mental Health Partnership NHS Trust; Black Country Healthcare NHS Foundation Trust; Cornwall Partnership NHS Foundation Trust; Gloucestershire Health & Care NHS Foundation Trust; Greater Manchester Mental Health NHS Foundation Trust; Humber Teaching NHS Foundation Trust; and Oxford Health NHS Foundation Trust. The trial is prospectively registered with the ISRCTN registry: ISRCTN79060696. The University of Oxford is the trial sponsor. There will be a data monitoring and ethics committee (DMEC).

**Figure 1 F1:**
[figure not shown]
Trial flow diagram. TAU, treatment as usual.

### Randomisation, blinding and code-breaking

Patients will be randomised once they have completed the baseline assessment. Randomisation, using an online system from Sealed Envelope (https://www.sealedenvelope.com/), will use a permuted blocks algorithm, with randomly varying block size, stratified by site.

The research assessors will be blind to group allocation, but the participants and staff members present will not be (they cannot be blinded to whether a psychological intervention is delivered or not). The gameChange staff deliverers (or trial co-ordinators) will inform patients of the randomisation outcome via telephone, to ensure the research assessors remain blinded to group allocation. Precautionary strategies to prevent unblinding of allocation include: the staff member and assessor considering room use and booking arrangements; patients being reminded by the assessor not to talk about their allocation result; and, after the initial assessment, the assessor not looking at the patient’s clinical notes. If an allocation is revealed between assessment sessions, this is logged by the trial coordinator and whenever possible, reblinding will occur using another assessor.

### Participants

The principal method of recruitment will be via the relevant clinical teams in the participating mental health services (eg, adult community mental health teams; early intervention services, inpatient units, mental health and well-being hubs, commissioned Voluntary, Community and Social Enterprise (VCSE). Recruitment can also be via research registers, where patients have given consent to be contacted about studies. As this is a real-world evaluation, clinical teams will be encouraged to use the Oxford Agoraphobia Avoidance Scale (O-AS)^8^ as part of routine assessment of patients with psychosis. This would identify people for whom gameChange may well be a suitable fit. It will also be the case that staff deliverers in the clinical teams, or Research Delivery Network research assistants embedded in the clinical teams, would be able to check eligibility against clinical notes.

Informed consent (see online supplemental materials) will be obtained from participants. This will be after provision of the patient information sheet (see online supplemental materials) to the patient, opportunities to ask questions, and at least 24 hours to decide. Our Lived Experience Advisory Panel (LEAP) has also emphasised the importance of patients in participating trusts being able to self-refer to the trial. This will minimise the chances that patients are overlooked by clinical teams or because their clinician was not present at a referral meeting. Hence, we will also advertise the study to patients via posters and leaflets in NHS buildings. However, in all instances, we will seek to confirm that a member of the clinical team gives approval for a patient to enter the trial and to complete the necessary check of eligibility and risk status. Written informed consent will be obtained from all participants.

The inclusion criteria are: participant is willing and able to give informed consent for participation in the trial; aged 16 years or older; attending NHS or commissioned VCSE mental health services; clinical diagnosis of schizophrenia spectrum psychosis or an affective diagnosis with psychotic symptoms; severe agoraphobic avoidance as assessed by the O-AS (score of 6 or above)^8^ and wanting help for that difficulty.

The exclusion criteria are: photosensitive epilepsy; in forensic settings or psychiatric intensive care unit; substantial difficulties in understanding or answering trial assessment questions; a participant may also not enter the trial if there is another factor (eg, current active suicidal plans that need to be the focus of intervention), which, in the judgement of the investigator, would preclude the participant from providing informed consent or from safely engaging with the trial procedures. Reason for exclusion will be recorded.

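### Unblinded gameChange deliverers may relay allocations and also check eligibility; under site-stratified blocks this modestly weakens allocation concealment

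*Protocol article*

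**What the plan says.** Three statements in the protocol article matter together.

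- **Who may screen.** Under Participants, "staff deliverers in the clinical teams, or Research Delivery Network research assistants embedded in the clinical teams, would be able to check eligibility against clinical" records. The wording permits this and does not require it. The same section adds that "in all instances, we will seek to confirm that a member of the clinical team gives approval for a patient to enter the trial" and completes an eligibility and risk check. It does not say that this team member must be someone other than a deliverer.
- **Who learns allocations.** Under Randomisation, blinding and code-breaking, "The gameChange staff deliverers (or trial co-ordinators) will inform patients of the randomisation outcome via telephone". A deliverer who makes these calls learns control as well as gameChange results. On blinding, "The research assessors will be blind to group allocation, but the participants and staff members present will not be".
- **How patients are allocated.** The online system "will use a permuted blocks algorithm, with randomly varying block size, stratified by site", and "Patients will be randomised once they have completed the baseline assessment".

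Some entry decisions call for judgement. The exclusion criteria end with an open category of other factors "which, in the judgement of the investigator, would preclude the participant from providing informed consent or from safely engaging with the trial procedures". The criteria also include wanting help with avoidance and substantial difficulty with the assessment questions.

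**The concern.** One role can sit on both sides of the randomisation: it may screen new patients and it may know where earlier ones went. The precautions listed against unblinding (room bookings, reminders to patients, keeping assessors away from the notes after the first assessment, re-blinding) all protect the outcome assessor. None of them covers the person who screens.

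Blocks within a site pull the running count back towards balance, so whoever knows that count can lean towards the right arm for the next patient. A deliverer who will treat the patient could, even without intent, put forward more promising patients when gameChange seems due. The analysis adjusts for site and the baseline value of the outcome. That deals with selection on baseline severity, but not with selection on motivation or other unmeasured prognosis. Such a bias would tend to favour gameChange and would be hard to detect afterwards.

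**Working it through.** The plan gives no figure for predictability, so there is none to reproduce.

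**Inputs from the article**
- 200 patients, 1:1, seven sites: 200/7 ≈ 29 per site.
- Five participants per therapist (Power calculation). Counting the gameChange arm only: 100/5 = 20 deliverers, 20/7 ≈ 3 per site. Counting waitlist patients too: 200/5 = 40 deliverers, 40/7 ≈ 6 per site.
- Planned 6-month O-AS avoidance difference: 5.4 − 3.2 = 2.2 points.

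**Assumptions, not in the article**
- Block sets 2/4/6, 4/6 and 4/6/8, with sizes equally likely.
- The share of earlier allocations that the screener knows.
- The number of other patients randomised between the check and the patient's own randomisation.
- A prognostic gap δ = 1 O-AS point between patients entered on a gameChange guess and those entered on a control guess.

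**Guessing rule.** Guess the arm with fewer known allocations so far at the site, and score ties as one half. Let g be the share of correct guesses. A patient in the gameChange arm was entered on a gameChange guess with probability g, and a control patient with probability 1 − g. With no treatment effect, the expected difference between arms is therefore δ × [g − (1 − g)] = δ × (2g − 1).

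**Simulated results, 29 patients per site**

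| Screener's knowledge | g | δ(2g − 1), δ = 1 |
|---|---|---|
| None | 50% | 0 |
| A third known, one patient in between | about 52% | 2 × 0.52 − 1 = 0.04 |
| A third known, no delay | about 54% | 2 × 0.54 − 1 = 0.08 |
| Half known, no delay | about 55% | 2 × 0.55 − 1 = 0.10 |
| All known, one patient in between | 57-59% | 0.14 to 0.18 |
| All known, no delay | 67.2% (4/6/8), 68.4% (4/6), 69.4% (2/4/6) | 0.34, 0.37, 0.39 |

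With all allocations known but three patients in between, g falls to 51-53% for these sets. A smaller block set, 2/4, would raise the worst case to 71.5%, or 2 × 0.715 − 1 = 0.43. A guesser who knows the set of block sizes and uses it optimally does no better than the simple rule, to within about 0.1 percentage point.

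Varying the block size limits certainty rather than prediction. With full knowledge the next allocation is certain for 2.5% (4/6/8) to 10.7% (2/4) of patients, against 32% with a fixed block of four.

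**Against the planned difference.** 0.04/2.2 ≈ 2%; 0.10/2.2 ≈ 5%; 0.39/2.2 ≈ 18%.

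**The case against.** A reader might infer that deliverers know every earlier allocation at their site and act as the gatekeeper, and so take the 0.34-0.39 points as the expected bias. The article does not support that. Trial co-ordinators may make the calls instead. Five participants per therapist implies roughly three to six deliverers per site, and nothing says that they share results.

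Delay is also built in. The notes check comes before the baseline assessment, and randomisation follows only once that is complete. Patients also have at least 24 hours to decide on consent. The screener does not control exactly when a patient enters the sequence.

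Nor is the deliverer shown to make the final decision. The open-ended exclusion rests with the investigator, the O-AS criterion is a score of 6 or above, patients can refer themselves, and reasons for exclusion are recorded. Online randomisation with varying, undisclosed block sizes is itself a concealment measure.

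All of this stands, and it reduces the size of the problem. Two replies remain. The clinical-team approval is not an independent check as written, because deliverers work in those teams and nothing bars one from giving it. And although sign-off of eligibility is often left to the full protocol or delegation log, the article goes further than silence: it assigns the screening task to a role that it elsewhere allows to learn allocations.

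**Conclusion.** The concern holds in a modest form. The stated roles allow someone who knows part of a site's allocation sequence to influence entry, so concealment is weaker than it need be. The likely advantage in guessing is a few percentage points above chance. It reaches 67-70% only if one screener knows everything and no other patient intervenes. For a 1-point prognostic gap the bias is about 0.04-0.10 O-AS points under partial knowledge and at most about 0.39 for the three block sets used.

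These figures rest on assumed block sizes, on assumed shares known, and on a gap that is illustrative and applied to every entry at every site. None of them alone would overturn a true 2.2-point difference. The article does not show that selection will occur, only that nothing in it prevents it. The change is worth making because it costs little and the planned adjustment cannot remove this kind of bias.

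**What to change.** In the Participants section:

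1. Limit gameChange deliverers to identifying and referring patients.
2. Have final eligibility, including the judgement-based exclusions, confirmed and locked in the database before randomisation by someone who does not know earlier allocations at that site. The blinded assessor who does the baseline could do this. So could a Research Delivery Network assistant, provided that person has no access to allocations.
3. State that the clinical-team approval and risk check come from a team member who is not a gameChange deliverer.

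If the screener knows no earlier allocation, g returns to 50% and the bias term to zero. If the full protocol or delegation log already separates these roles, it is enough to say so.

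Cost: wording in the protocol and delegation log, using roles already in the trial. The downside is a possible short delay at small sites, where a deliverer could no longer sign off eligibility alone.
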